## Methods

### Study design

This trial is a prospective, single center, randomized controlled trial. The study is conducted the Amphia hospital Breda, one of the largest teaching hospitals in the Netherlands. Four shoulder specialists represent the Upper Limb Unit and will participate in the trial.

### Recruitment and consent

All adult patients presenting to the outpatient with the clinical diagnosis of a FS in stage two will be invited to participate in the trial. A general history is acquired. The upper extremity is examined and range of motion is measured. Conventional radiographs (true anteroposterior in the scapular plane, internal rotation with 90 degrees of flexion in the elbow and the forearm in front of the abdomen, and in maximal external rotation) are made at baseline, to rule out other pathology such as osteoarthritis. The treating orthopaedic surgeon or a member of the study staff will introduce and explain the trial to the patient and address any further questions. The patient will receive a written information leaflet together with an informed consent form. After ample time to consider participation in the trial, patients return to the outpatient clinic. After receiving verbal and written consent, eligible patients will be randomized. A secure web based randomization program (CASTOR, https://www.castoredc.com/) is used for block randomization with differing block sizes and with a randomization allocation ratio of 1. This randomization schedule is only accessible for the research coordinator. Applicants will be allocated to either the MUA group or the PT group. Only the research coordinator (who is not a treating physician) will be authorized to use the randomization software module in CASTOR to allocate patients to their intervention group, hereby ensuring concealed allocation. A participant flow diagram is shown in Fig. 1. Blinding of patients is not possible. Range of motion measurements are done by a nurse practitioner, blinded for the intervention. Crossing over (from PT to MUA) is potentially possible because patients are allowed to quit participation in the trial as a personal choice. However, the results will be analysed based on the initial treatment allocation using the intention to treat (ITT) analysis (see ‘statistical analysis’ section for more details).

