### Intervention

Patients assigned to the MUA group will be scheduled for the intervention within approximately 2–6 weeks (generally within 2 weeks). MUA is performed by one orthopaedic surgeon (RB) at the recovery room under single shot interscalene brachial plexus block. The interscalene block is administered by the anesthesiologist using ultrasound guidance. Levobupivacaine 0.375% is used, and a ‘soak time’ of approximately 45 min is pursued. If necessary or desired by the patient, general anesthesia can be added. The scapula is indirectly stabilized by the supine position, a short lever arm and 90 degrees of elbow flexion is used to prevent fractures and brachial plexus traction injuries. The glenohumeral joint is forced through a full range of motion in a strict pattern: anteflexion - > abduction, external rotation in 90 degrees’ abduction- > internal rotation in 90 degrees’ abduction - > horizontal adduction with dorsal compression and external rotation in neutral. A recognizable tearing sound is typically present when dealing with a FS. This sequence can be repeated until full range of motion is acquired. Postoperative physiotherapy is started directly on the same day (within 4 h after MUA) to maintain the acquired full range of motion. People stay at the orthopaedic ward for one night. The first week after MUA, patients have to visit a physiotherapist on a daily basis. The physiotherapy treatment is individualized in the need of the particular patient and it’s possibilities in ROM and dysfunction after a long period of stiffness. Therapy will exist of mobilizations in all end ranges known in arthrokinematics of the shoulder which are the same used by the orthopedic surgeon during MUA. Mobilizations are applied in (Maitland) grade 3, 4 or even 5 if necessary. This means that end feel is reached even if painful. The target is to reach the same end range as reached by the orthopedic surgeon after MUA, or the best possible after anesthetics are worked out. It is continuously tried to be within the pain area of NRS 0 to 5 or even up to NRS 7 for a short period of time, but only then when the pain vanishes within one or 2 h after therapy. The goal is to give the maximum of stimulus which the patient can handle. Therefore, the frequency of therapy is high, but the period of inflammation after manipulation is respected. Patients are given a home exercise program to maintain ROM which they have to imbed in their daily activities. The exercises will mainly concern stretching in different angles with a total end range time of at least 2 min. After 2 weeks, if ROM is maintained, a general exercise program is applied to regain function of cuff and scapular muscles (using elastic exercise bands or halters) with the goal to return to normal shoulder girdle function.

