### Study procedures

At 1, 3 months and 1 year, relevant outcome data are collected through clinical evaluation performed by the trained nurse practitioner, an orthopaedic surgeon, or resident in orthopaedic surgery. The range of motion is measured by a trained nurse practitioner who is blinded for the intervention. In the MUA group, the first follow up time is 1 month after the intervention. In the PT group, the first follow up time is 1 month after allocation. The schedule of enrolment, interventions, and assessments is shown in Fig. 4. The duration of the physiotherapy program in both groups is variable and depends on the individual result and desire of the patients. It is up to the patient to discuss this with their individual physiotherapist.

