### Statistical analysis

All data will be analysed in an encoded fashion. We will use CASTOR (https://www.castoredc.com/), an online data-management program, designed for medical research purposes. The patient’s demographic characteristics, EQ-5D score, range of motion at baseline, duration of symptoms before treatment starts and diabetes mellitus will be summarized and compared between groups. Also the distribution of all patient’s outcome variables will be summarized by treatment group and by time. The summaries will consist of the following descriptive statistics: number of patients involved, mean and standard deviation (or median and (inter quartile range when appropriate) for continuous variables and relative frequencies (percentages) for categorical variables. We will report the number of participants (denominator) included in each analysis and the Intention To Treat principle will be used with respect to group assignment. So, the final results of the patients will be analysed in the group to which they were allocated at the start of the study.”

The SPADI-measurements will be analysed using linear mixed modelling. The restricted maximum likelihood technique will be used for estimating the model parameters. The independent variables are time (3 levels: 1, 3 and 12 months) and treatment (2 levels), as well as their interaction. The following baseline covariates will also enter the model: SPADI at baseline, diabetes and duration of symptoms before intervention.

Primary efficacy measure is the treatment effect (MUA vs. PT) on total SPADI score after 1 month. This effect is estimated as contrast on the coefficients of the linear mixed model including the treatment-by-time interaction as mentioned above. Missing values in patients with incomplete observations will be appropriately dealt with by using the restricted maximum likelihood technique. Secondary efficacy measures are the treatment effects after 3 and 12 months and an average treatment effect over time obtained by deleting the treatment-by-time interaction. In addition, this interaction will be tested as part of the secondary efficacy analysis. Other secondary continuous outcome variables, such as OSS, NPRS, EQ-5D, WORQ-UP and ROM, will be analysed similarly to SPADI, with the baseline measurement of the outcome variable at hand as covariate. When appropriate, the outcome variable will be transformed so as to obtain normally distributed residuals.

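### The article describes crossover from PT to MUA as quitting the trial, promises intention-to-treat analysis, and does not say these patients are still measured

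*Protocol article*

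**What the plan says.** In Recruitment and consent the article explains how a PT patient may come to have the manipulation: "Crossing over (from PT to MUA) is potentially possible because patients are allowed to quit participation in the trial as a personal choice". The next sentence reads: "However, the results will be analysed based on the initial treatment allocation using the intention to treat (ITT) analysis", and points to Statistical analysis for details.

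Statistical analysis restates the allocation rule: "the final results of the patients will be analysed in the group to which they were allocated at the start of the study". On incomplete data it says: "Missing values in patients with incomplete observations will be appropriately dealt with by using the restricted maximum likelihood technique". The model has three post-baseline times (1, 3 and 12 months), treatment and their interaction, with baseline SPADI, diabetes and symptom duration as covariates. The primary contrast is fixed at the first visit: "Primary efficacy measure is the treatment effect (MUA vs. PT) on total SPADI score after 1 month". The 3- and 12-month contrasts are secondary.

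Study procedures gives the visits ("At 1, 3 months and 1 year, relevant outcome data are collected through clinical evaluation") and starts the PT clock at randomisation: "In the PT group, the first follow up time is 1 month after allocation". It does not say whether a patient who has crossed over still attends them.

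**The concern.** Intention to treat settles which group a patient is counted in. It does not supply an outcome for a patient who is no longer measured. Read plainly, quitting participation ends data collection, so the crossover sentence and the intention-to-treat sentence pull against each other. The statistical section repeats the allocation rule without resolving this.

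In this trial the loss would probably be related to outcome. Patients enter because an injection and at least six weeks of physiotherapy had not helped enough, and the PT arm continues physiotherapy. Patients know their allocation, and manipulation is in regular use at the same hospital (89 patients in two years, per the Background). Those who leave PT for MUA are likely to be those doing badly.

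If their later SPADI scores are missing, the PT arm looks better than the policy of starting with PT really is, and the benefit of MUA is understated at 3 and 12 months. The article itself declines to draw firm conclusions from the one earlier randomised trial because of heavy loss to follow-up.

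**Working it through.** **Plan's own figure.** Inputs from Sample size calculation: difference 13, SD 17, power 90%, alpha 0.05 (taken as two-sided), 10% dropout. Normal approximation: n = 2 × (1.960 + 1.282)² × (17/13)² = 35.9, so 36 per group; 36/0.9 = 40. The t-test version gives 36.9, so 37; 37/0.9 gives 42 and 37 × 1.10 gives 41. The stated 41 is reproduced to within rounding and choice of formula. The issue is not a sample-size error.

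**Which visits are exposed.**
- A patient who crosses over after month 1 already has the primary SPADI. That value stays in the mixed model, and only the 3- and 12-month values are at risk.
- A patient who quits before month 1 has no post-baseline value. Baseline SPADI is a covariate, so this patient contributes no outcome to the model at all.
- The PT month-1 visit is one month after allocation. Even patients allocated to MUA wait about 2–6 weeks, usually no more than 2, so quitting before month 1 means leaving almost at once.

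**Loss of numbers.** Take 41 randomised per group and 10% loss in the MUA arm (36.9 left). With 10% of PT lost (36.9 left), SE = 17 × √(1/36.9 + 1/36.9) = 3.96 and power is 0.91. With 20% lost (32.8 left), SE = 4.08 and power is 0.89. Power is hardly affected; bias is the matter to size.

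**Bias.** The crossover fraction q is not in the documents, so 10% and 20% are assumptions. Higher SPADI is worse.

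1. If the worst fraction q of PT patients is unobserved, the mean of the rest is too low by SD × φ(z)/(1 − q), where z is the (1 − q) normal quantile.
 - q = 0.10: 17 × 0.1755/0.90 = 3.3
 - q = 0.20: 17 × 0.2800/0.80 = 5.9
2. If leaving correlates only 0.5 with outcome, halve these: 1.7 and 3.0.
3. These shifts compare with the scores patients would have had without crossing over. Under intention to treat the target is the policy as allocated, in which crossovers count with their scores after MUA. If each gains the protocol's 13 points (an assumption), the true PT policy mean itself improves by 13q: 1.3 at 10%, 2.6 at 20%.
4. Bias against the policy target = shift − 13q, from unrounded shifts:

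| | 10% cross over | 20% cross over |
|---|---|---|
| Worst patients leave | 3.32 − 1.30 = 2.0 | 5.95 − 2.60 = 3.3 |
| Correlation 0.5 | 1.66 − 1.30 = 0.4 | 2.97 − 2.60 = 0.4 |

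All four are before any recovery from baseline SPADI and earlier visits, which the mixed model uses.

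**If crossovers are kept under PT.** With the same 13-point gain, the as-allocated difference becomes 13 × (1 − q): 11.7 at 10% and 10.4 at 20%. With 36.9 per group, power is 0.84 and 0.75. That dilution is part of the as-allocated effect and concerns visits after the crossover.

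**The case against.** The strongest reply is that the article never says data collection stops at crossover. Its two intention-to-treat sentences suggest that crossovers' results are expected to be available, and rules for follow-up after stopping treatment may sit in the full protocol, which is not shown. This stands in part. A reader might infer that crossover is possible only by quitting, that the outcomes are lost, or that the intention-to-treat analysis cannot be carried out. The text supports none of these. The word only is not there, loss is an inference from quitting, and scores recorded before a patient leaves stay in the model under the allocated group. What remains is not mere missing detail: the article states a crossover route, and that route conflicts with its own analysis principle.

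It is also fair that the primary contrast is little exposed and that restricted maximum likelihood is not useless here. Leaving because a recorded month-1 score is poor is missingness that depends on observed data, which the method handles. It does not handle leaving because of worsening since the last recorded visit.

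Finally, the article lets patients in general quit. It names PT to MUA only as the direction of crossover, so it does not establish that departures come from one arm alone.

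**Conclusion.** The point holds as an unresolved conflict between two adjacent sentences. Its consequence falls mainly on the secondary 3- and 12-month contrasts, and on month 1 only for patients who quit before that visit.

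If quitting ends measurement, the likely direction is to understate the benefit of MUA. With SD 17, 10% (20%) crossing over and a 13-point gain after MUA, the bias against the as-allocated effect is at most about 2.0 (3.3) points, and about 0.4 at either rate if leaving correlates 0.5 with outcome. The design difference is 13. A reader might take the 3.3 (5.9) points of step 1 as the bias. They measure departure from a world without crossover, which is not what an intention-to-treat analysis estimates; they would apply only if crossovers gained nothing from MUA.

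The crossover rate, the gain and the correlation are all assumed, so these figures give a scale and not a forecast. The matter is worth correcting because outcomes not collected cannot be recovered later. It does not by itself undermine the primary result.

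**What to change.** Reconcile the two sentences by separating stopping the allocated treatment from withdrawing from follow-up. State that:

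- a PT patient who has MUA remains in the trial;
- this patient completes SPADI and the other outcomes on the original 1-, 3- and 12-month dates, counted from allocation, and is analysed under PT;
- only withdrawal of consent for data collection ends follow-up;
- the date of crossover is recorded.

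This concerns data collection and analysis only and leaves treatment decisions as they are. The cost is a change to protocol and consent wording and continued questionnaires for a few patients. If the sponsor already intends to follow these patients, it is a correction of wording alone.

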**Fig. 1 Fig1:**
[figure not shown]
Participant flow diagram

If patients visit the outpatient clinic with a stage one FS, they are not (yet) eligible for inclusion in the study. A standardized treatment regimen will be followed, as is the current usual care. They are given advice and education about the condition, the prognosis and the possible treatment options are discussed. An informative brochure and referral to a physiotherapist with instructions is given. An intra-articulair corticosteroid infiltration is discussed and directly administered if desired. Information about the trial is provided. Evaluation takes place after 3 months at the outpatient clinic and eligibility for inclusion in the study will be reassessed.

### Study population

This study focusses on patients with a clinical diagnosis of a stage two FS. This is defined as symptoms of pain and stiffness, predominantly in one shoulder, persisting ≥3 months, without preliminary trauma which led to an anatomic abnormality. Characteristically, the pain is most severe at the end of the range of motion. Pain must be diminished compared to the maximum amount of pain in stage one of the condition.

In order to be eligible to participate in this trial, patients must meet all of the following criteria:Age > 18 years and ≤70 yearsRestriction of passive motion in the glenohumeral joint of ≥30° in external rotation and at least a second plane of movement with ≥30°restriction (compared to the contra-lateral side)Unsuccessful conservative therapy within the previous 3 months. This is considered as insufficient improvement after an intra-articular corticosteroid infiltration and physiotherapy treatment during at least 6 weeks.

Patients with diabetes are eligible for participation in this trial.

If any of the following criteria will apply, patients will be excluded from participation:Numeric Pain Rating Scale at rest ≥7Onset of symptoms ≥1 year agoOsteoarthritis of the glenohumeral joint, Kellgren-Lawrence osteoarthritis grading scale ≥2Previous surgery to the shoulderSystemic inflammatory joint diseaseEvidence of a complete rotator cuff tear on physical examination, ultrasound images or MRINeurological disorders of the upper limbTherapeutic anticoagulation which can not be interrupted without bridging therapyOther known shoulder pathology such as infection or tumorContra-indication to corticosteroid injection, allergy to contrast or local anaestheticInability to give informed consent and fill out questionnaires

### Intervention

Patients assigned to the MUA group will be scheduled for the intervention within approximately 2–6 weeks (generally within 2 weeks). MUA is performed by one orthopaedic surgeon (RB) at the recovery room under single shot interscalene brachial plexus block. The interscalene block is administered by the anesthesiologist using ultrasound guidance. Levobupivacaine 0.375% is used, and a ‘soak time’ of approximately 45 min is pursued. If necessary or desired by the patient, general anesthesia can be added. The scapula is indirectly stabilized by the supine position, a short lever arm and 90 degrees of elbow flexion is used to prevent fractures and brachial plexus traction injuries. The glenohumeral joint is forced through a full range of motion in a strict pattern: anteflexion - > abduction, external rotation in 90 degrees’ abduction- > internal rotation in 90 degrees’ abduction - > horizontal adduction with dorsal compression and external rotation in neutral. A recognizable tearing sound is typically present when dealing with a FS. This sequence can be repeated until full range of motion is acquired. Postoperative physiotherapy is started directly on the same day (within 4 h after MUA) to maintain the acquired full range of motion. People stay at the orthopaedic ward for one night. The first week after MUA, patients have to visit a physiotherapist on a daily basis. The physiotherapy treatment is individualized in the need of the particular patient and it’s possibilities in ROM and dysfunction after a long period of stiffness. Therapy will exist of mobilizations in all end ranges known in arthrokinematics of the shoulder which are the same used by the orthopedic surgeon during MUA. Mobilizations are applied in (Maitland) grade 3, 4 or even 5 if necessary. This means that end feel is reached even if painful. The target is to reach the same end range as reached by the orthopedic surgeon after MUA, or the best possible after anesthetics are worked out. It is continuously tried to be within the pain area of NRS 0 to 5 or even up to NRS 7 for a short period of time, but only then when the pain vanishes within one or 2 h after therapy. The goal is to give the maximum of stimulus which the patient can handle. Therefore, the frequency of therapy is high, but the period of inflammation after manipulation is respected. Patients are given a home exercise program to maintain ROM which they have to imbed in their daily activities. The exercises will mainly concern stretching in different angles with a total end range time of at least 2 min. After 2 weeks, if ROM is maintained, a general exercise program is applied to regain function of cuff and scapular muscles (using elastic exercise bands or halters) with the goal to return to normal shoulder girdle function.

Patients allocated to the PT group are given advice and education about the natural course of the disease. A corticosteroid injection in the glenohumeral joint of kenacort 40 mg (1 ml) and chirocaine (4 ml) is given within the first 3 months of the condition, thus this will be done before inclusion in the study is possible. When the pain is not sufficiently diminished, this can be repeated. An advice for physiotherapy is given with a written protocol to hand out to their physical therapist based on the recent guideline of the Dutch Shoulder Network for the treatment of frozen shoulders (Fig. 2). This guideline uses a categorization in “tissue reactivity” with parameters of pain and ROM [16] that guides the treatment intensity and strategy (Fig. 3). A variety of treatments is used including, passive stretching, mobilisation techniques, active scapulothoracic exercises and cuff exercises. The Duration of physiotherapy treatment depends on the individual progression.

**Fig. 2 Fig2:**
[figure not shown]
Determination of tissue reactivity in Frozen Shoulder

**Fig. 3 Fig3:**
[figure not shown]
Treatment strategy guideline based on tissue reactivity

### Outcome measures

The primary objective of this study is to evaluate the difference in functional outcome after treatment of a FS with or without MUA, measured by the SPADI at 1 month compared to baseline. The SPADI is a self-reported questionnaire, with 13 questions responded on a ten-point scale divided in two domains: pain (5 items) and disability (8 items). A total SPADI score is calculated by summing up all 13 items and dividing by 130 (the maximum score) times 100. This leads to a score between 0 (best) and 100 (worst) [27]. The SPADI has been translated and validated in Dutch [28, 29].

Secondary outcome measures consist of;Oxford Shoulder Score (OSS), which reflects both function and pain of the shoulder. The OSS is a patient reported questionnaire, which consist of 12 questions related to pain and function of the arm in daily life. Items are scored on a zero to four point scale. This leads to an OSS score between 0 (worst) and 48 (best) [30].Shoulder pain at rest, and during activity; Pain level will be determined using the The Numeric Pain Rating Scale (NPRS). The NPRS is a validated 11-point score to assess pain, which represents a valid measure of pain with a good construct validity. The NPRS ranges from zero to ten, in which zero expresses no pain and ten expresses the worst pain possible.Health related quality of life, determined using the three level EuroQol five-dimensional questionnaire (EQ-5D 3-L). The EQ-5D is a five question standardised questionnaire scoring on five domains: mobility, self-care, usual activities, pain/discomfort, and anxiety/depression. It also includes a VAS self rating health scale on which patients rate their health state (0 is worst imaginable health and 100 is best imaginable health) [31]Passive Range of Motion (ROM) is measured by a goniometer. Forward flexion and abduction in the standing position, external rotation measured with the arm held at the side and the elbow in 90° flexion. Internal rotation is estimated to which height the patient can reach on his back, appointed to the highest vertebral level of the wrist.The ability to work is evaluated by two questionnaires. The WORQ-UP is a patient reported questionnaire with 17 items of common physical tasks at work, scored on a five point scale [32]. Single item work ability Index is a single question whereby patients rate their ability to perform physical tasks at work on a ten point scale. Zero indicates no ability to perform work with any physical task at all. Ten indicates the best period in life to perform physical tasks at work [33–35]. Absenteeism at work is evaluated with a single question where patients register the amount of days absent at work past month due to complaints of the shoulder.Duration of symptoms is determined. Patients are asked to estimate the duration of symptoms in weeks from MUA or allocation to the PT group until almost full recovery.Two anchor questions will be asked regarding the change that is experienced since the start of treatment considering pain and daily functioning. This is reported on a seven-point scale. These questions are based on an advice to use them from the division shoulder and elbow from the Dutch Orthopaedic Society.Quantity of physiotherapy treatment sessionsUsage of analgesics (acetaminophen, NSAID’s or opioids)Number of repeated corticosteroid infiltrationsNumber of complications (infection, fracture, dislocation, neurovascular compromise, subsequent or intervention) will be registered and evaluated.

Passive range of motion is the only blinded outcome measure. All other outcomes are assessed unblinded or self reported.

